## Abstract

**Background:**

Challenging behaviours, in particular aggressive behaviours, are prevalent among people with intellectual developmental disabilities. Predictors of challenging behaviours are numerous, including past history of aggression, poor coping skills and impulsivity. Factors like motor or rapid-response impulsivity (RRI) have neurobiological underpinnings that may be amenable to change via neuromodulation using non-invasive brain stimulation techniques like transcranial direct current stimulation (tDCS).

**Methods:**

This study aims to determine the efficacy of anodal tDCS in reducing RRI and incidents of aggression in people with intellectual developmental disabilities (IDD) in residential or hospital settings. Using a single blind, randomised, sham-controlled trial design, adults with IDD, with a history of impulsivity leading to aggression, will be randomised to receive either repetitive anodal or sham tDCS applied to the left dorsolateral prefrontal cortex. Outcome measures assessing impulsivity and aggression will be collected for up to 1 month following the last tDCS session.

**Discussion:**

The results of this study may pave the way for developing targeted interventions for impulsivity and aggressive behaviours in people with IDD.

## Administrative information

Note: the numbers in curly brackets in this protocol refer to SPIRIT checklist item numbers. The order of the items has been modified to group similar items (see https://can01.safelinks.protection.outlook.com/?url=http%3A%2F%2Fwww.equator-network.org%2Freporting-guidelines%2Fspirit-2727-statement-defining-standard-protocol-items-for-clinical-trials%2F&data=04%7C01%7Cnrk2%40queensu.ca%7C7a5979f36f7f43b5866608da0eff7c2b%7Cd61ecb3b38b142d582c4efb2838b925c%7C1%7C0%7C637838787710809005%7CUnknown%7CTWFpbGZsb3d8eyJWIjoiMC4wLjAwMDAiLCJQIjoiV2luMzIiLCJBTiI6Ik1haWwiLCJXVCI6Mn0%3D%7C3000&sdata=PhMQm49uQnZT6a8rgoUxl70CjCar1zaViVyyqTgQGmI%3D&reserved=0).

## Introduction

### Background and rationale {6a}

Challenging  behaviours are common among people with intellectual developmental disabilities (IDD), encompassing behaviours such as aggression, sexually inappropriate behaviours, self-injury, and criminality [1]. Research studies reported an overall prevalence rate of 10–15% for any type of challenging behaviour [2] and rates ranging from 6.1% in community settings to 40% in long-stay hospitals with significant adverse consequences, e.g. in terms of quality of life, legal consequences, breakdown of placements, and harm to others [3].

The aetiology of aggressive behaviours is multi-factorial, including physical complaints (e.g. pain, constipation, infection), behavioural phenotypes (e.g. Prader Willi syndrome), psychiatric disorders (e.g. psychosis, autism spectrum disorder), and psychosocial factors like trauma [3]. Predictors of inpatient aggression among people with IDD are numerous, including past history of aggression, poor coping skills, and impulsivity [4, 5]. Some factors, like impulsivity, have defined neurobiological underpinnings that are amenable to change through biopsychosocial interventions.

A multi-dimensional construct with cognitive, motor, and temporal dimensions [6, 7], impulsivity reflects a tendency to act without thinking through the consequences of one’s actions. Motor or rapid-response impulsivity (RRI) is a form of impulsivity that reflects failure to refrain from action initiation or to stop an ongoing or prepotent action [8]. RRI underpins several psychiatric disorders including borderline personality disorder, attention deficit hyperactivity disorder, and substance use disorders. Due to its association with criminality, poor concordance with treatment, and suicidality, impulsivity is regarded as an important consideration in risk assessment and management [6, 9–12]. Although numerous biopsychosocial approaches have been proposed to manage aggression and impulsivity in people with IDD [3, 13], the evidence base for their efficacy is limited, highlighting the need to develop specific or adjunctive interventions.

Transcranial direct current stimulation (tDCS) has been used to modulate impulsivity with some promising results [7, 14, 15], offering great potential as a treatment modality for impulsive and aggressive behaviours in people with IDD. In their review of the literature on the use of non-invasive brain stimulation (NIBS) techniques, including tDCS, to modulate impulsivity in healthy subjects, Brevet-Aeby and colleagues [14] reported that tDCS can effectively modulate key facets of impulsivity including inhibitory control and delay discounting. A more recent review by Yang and colleagues [7] indicated that tDCS has a significant, albeit small, effect on modulating impulsivity in people with mental disorder. TDCS can be used to modulate a brain network involving the left dorsolateral prefrontal cortex (DLPFC) and limbic system (anterior insula, amygdala, anterior cingulate cortex). Disruption to this network, with reduced ‘top-down’ control from the DLPFC and an overactive limbic system, results in greater impulsivity [12]. Iwabuchi et al. [16] modulated this network using intermittent theta burst stimulation (iTBS) applied to left DLPFC, whereby iTBS significantly dampened fronto-insular effective connectivity. This mechanism might underpin the therapeutic effects of tDCS in reducing impulsivity.

### Objectives {7}

This study is the first randomised controlled clinical trial that aims to assess the efficacy of anodal tDCS in reducing RRI and incidents of aggression in people with IDD. We hypothesise that anodal tDCS applied to the left DLPFC will result in greater reductions in impulsivity and incidents of aggression than sham tDCS, demonstrating a clear treatment effect of tDCS in persons with IDD. Here, we outline the experimental protocol used to address our hypotheses.

### Trial design {8}

A single blind, parallel arms, randomised controlled trial design will be employed in this study. The trial is explanatory in nature and this type of trials aims to assess the efficacy of an intervention (i.e. tDCS) under controlled conditions that are well-defined [17].

## Methods: participants, interventions, and outcomes

### Study setting {9}

The study involves adults with mild IDD residing in the community, inpatient units, or care homes in the Southern Ontario Region of Canada.

### Eligibility criteria {10}

The inclusion criteria are as follows: (i) adults aged between 18 and 65 with mild IDD, (ii) a history of at least one incident of aggression in the last month, and (iii) consent to participate in the trial by the individual or their substitute decision-maker if they lack the capacity to consent to participate in research.

The exclusion criteria are as follows: (i) a history epilepsy, significant head injury or other neurological conditions, or brain surgery; (ii) having a metal in the brain or skull, a cardiac pacemaker, a central line, or a cochlear implant; (iii) current history of drug or alcohol misuse; and (iv) a history of adverse reaction to tDCS or having a sensitive scalp. Table 1 provides more information about the inclusion and exclusion criteria. A tDCS safety questionnaire will be administered to identify those who meet the exclusion criteria.

**Table 1 Tab1:** Inclusion and exclusion criteria

Inclusion criteria	Exclusion criteria
Adults aged 18–65 years	History of epilepsy or seizures
Diagnosis of a mild intellectual developmental disability	History of acquired brain injury
History of 1 or more incidents of aggression in the last month	Having metal in the brain/skull, e.g. splinters, fragments, or clips
Consent to participate in the trial by the individual or their substitute decision-maker	Having a cochlear implant
	Having an implanted neuro-stimulator (e.g. direct brain stimulation, epidural/subdural stimulation, vagal nerve stimulation)
	History of brain surgery or procedure
	History of severe adverse reaction to tDCS
	Having a cardiac pacemaker or intracardiac lines
	Current alcohol or drug misuse
	Having a sensitive scalp

### Who will take informed consent? {26a}

In Canada, research ethics boards review applications in accordance with the principles set out in the “Tri-Council Policy Statement: Ethical Conduct for Research Involving Humans – TCPS 2 (2018)” [18]. TCPS defines decision-making capacity as “… the ability of prospective or actual participants to understand relevant information presented about a research project and to appreciate the potential consequences of their decision to participate or not participate.” (P.44) [18]. TCPS stipulates that for research involving individuals who lack capacity to consent, researchers should seek and maintain consent from an authorised third party, often referred to a substitute decision-maker (SDM), in accordance with the best interests of the individual concerned. In Ontario, the assignment of SDMs is governed either under the Substitute Decisions Act or the Health Care Consent Act based on either a treatment, personal, or financial decision and level of IDD does not preclude capacity to consent until formally queried and then an SDM is assigned. Hence, we would assume for the trial that potential participants will be deemed able to consent unless a SDM is already assigned or a Public Guardian Trustee is assigned due to no family members being accessible.

Members of the research team are acutely aware of the ethical issues regarding the enrolment of participants who lack capacity to consent to participate in research. The core ethical principles underpinning the TCPS policy on research will be adhered to, namely, respect for persons, concern for welfare, and justice [18].

The study will recruit participants [henceforth, the term ‘participant’ will be used throughout the protocol to refer to individuals with IDD undergoing the intervention] from intellectual developmental disability services in the Kingston area (or Southern Ontario Region). Posters will be placed publicly at Resource Centres in Kingston, and community living spaces where people with IDD reside. Participants will be identified by their psychiatrist, caregiver, or support worker. Capacity to consent to participate in research will be determined by the individual’s treating psychiatrist. Individuals designated to identify potential participants will ask prospective participants or their substitute decision-maker to complete a hospital “consent to be contacted for research” form. Study personnel (a research assistant or study coordinator) will then contact the individuals who have already consented to be contacted for research purposes either in person at the health service, by phone, or by email. If an individual is unable to provide consent, their substitute decision-makers will be approached. Study personnel will ensure that potential participants have not opted-out or withdrawn their consent or provided consent to be contacted for research purposes before initiating contact with participants or their substitute decision-makers.

Designated study personnel will review or read over the consent with the participant or their substitute decision-maker and answer any questions they have. Individuals must be able to understand that participation is completely voluntary and they can withdraw consent at any time and without giving a reason. To minimise coercion in the consenting process, the participant letter of information has been adapted to a grade 3 reading/comprehension level. The letter provides information about the side effects of tCDS using a simple language with visual aids. For example, it explains about tingling as follows: “A lot of people feel a tingling feeling under the pads. It should not hurt. This is felt when the electricity is turned on and just after. It is not scary.”

New information will be shared with participants and their substitute decision-makers at any time during their participation in the study as soon as it becomes available. Participants will be re-consented if necessary during the study at any study visit and the study will not proceed until the participant is re-consented. Participants or their substitute decision-makers can withdraw their consent at any time by expressing their desire to do so to study personnel.

### Additional consent provisions for collection and use of participant data and biological specimens {26b}

Not applicable.

## Interventions

### Explanation for the choice of comparators {6b}

The comparator is sham tDCS stimulation. The fundamental principle of a sham stimulation is that participants struggle to unblind themselves to the treatment. Ten seconds of stimulation is sufficient to keep individuals blinded to their treatment arm but is not enough stimulation to modulate brain activity. The validity of this sham protocol has been previously demonstrated [17].

### Intervention description {11a}

The Soterix tDCS kit [19] will deliver 20-min stimulation sessions using two 5×5 cm sponge electrodes. The stimulation montage will comprise left DLPFC anodal or sham stimulation. The anodal electrode will be placed over the area corresponding to the left DLPFC (F5 of the EEG10–20 international system) and the reference (cathodal) electrode over the right supraorbital ridge. The active stimulation condition will use a constant current of 2mA, delivered via current ramps over 10 s at the onset and offset of stimulation, respectively. For sham stimulation, the current will be delivered only in the first 10 s, after which the stimulation will cease but with the electrodes still in place throughout the session.

The intervention will be delivered in a private room at Providence Care Hospital in Kingston Ontario or at the residential home where the participant is residing if they are unable to travel. The intervention will be delivered by a research assistant under the supervision of the principal investigator.

### Criteria for discontinuing or modifying allocated interventions {11b}

Discontinuation rules for individual participants include withdrawal of consent, development of a coincidental health problem/illness, or exacerbation of aggressive behaviours expressed as a report of a serious violent incident and/or an increased incidence of self-harm or self-injurious behaviour as judged by their caregivers. Additionally, the study could stop early if the intervention significantly exacerbates aggressive, impulsive, or self-harming behaviours as judged by the trial investigators.

### Strategies to improve adherence to interventions {11c}

tDCS stimulation will be administered by a research assistant as per the study protocol. The research assistant will hold an undergraduate degree in health or social sciences. They will receive adequate training on the administration of the study protocol including tDCS. The principal investigator, who has expertise in tDCS, will provide the necessary training. To ensure adherence to the study protocol, two dummy runs will be conducted at the start of the trial, and these will involve the administration of the study questionnaires and tDCS. Additionally, the principal investigator will directly supervise the administration of the study protocol for the initial experiments that will involve participants.

### Relevant concomitant care permitted or prohibited during the trial {11d}

The participants will continue to receive usual care from mental health services or other support agencies for people with intellectual developmental disabilities. It is anticipated that the level of usual care will vary according to the need of the individual, and may include pharmacological and psychosocial interventions, some of which may target impulsivity and aggressive behaviours. It is envisaged that randomisation would counter balance the effects of these interventions across the study arms, such that additional effects could be attributed to tDCS.

### Provisions for post-trial care {30}

Patients will be informed what arm (treatment or sham) they were allocated to at the end of the study. They will also be advised to contact the study's principal investigator should they experience any adverse effects following each session. Additionally, participants will continue to receive usual care at the discretion of the treating psychiatrist or care team. It usually involves a combination of behavioural approaches, psychosocial interventions, and psychotropic medications.

### Outcomes {12}

#### Primary outcome measure

##### Aggression

The *Modified Overt Aggression Scale* (MOAS) [20] will be used as a repeated measure to assess aggressive behaviours at baseline, 1 week (day 10), and 1 month (day 38) following the last tDCS treatment. MOAS is an informant-rated scale which will be completed by a member of care staff who have professional knowledge of the participant. MOAS has four domains (Verbal Aggression, Aggression Against Property, Autoaggression, and Physical Aggression) which are weighted and each rated on a 5-point scale (0–4). Scoring of MOAS yields weighted scores, total and by domain. MOAS is considered to be a reliable measure of aggressive behaviours in people with IDD [21].

##### Maladaptive behaviours

*The Behavior Problems Inventory Short Form* (BPI-S) [23] is an informant-rated instrument which is used to assess maladaptive behaviours in people with IDD. Changes in maladaptive behaviours will be measured at baseline, 1 week (day 10), and 1 month (day 38) following the last tDCS treatment. BPI-S is a 30-item scale that assesses behaviour problems on three domains: self-injurious, aggressive/destructive, and stereotyped behaviours. It is a repeat measure in which scoring yields total and domains scores for frequency for all domains as well as severity scores for self-injurious and stereotyped behaviours domains. It measures frequency on a 5-point scale (0=never/no problem, 1=monthly, 2=weekly, 1=daily, 4=hourly). It measures severity on a 3-point scale (1=mild, 2=moderate, 3=severe). BPI has been developed for use in people with IDD with good psychometric properties [24].

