## Statistical methods

### Statistical methods for primary and secondary outcomes {20a}

Behavioural outcome measures will be analysed using the Statistical Package for Social Sciences (SPSS; Version 26). A 2 × 2 Repeated Measures ANOVA will be performed with group allocation (active tDCS vs. sham tDCS) and time (pre- vs. post-tDCS stimulation). Post tDCS measures for MOAS, SST, and BPI-S will be treated separately as repeated measures. Total scores on BIS-11 will be entered into the analysis as a covariate. Significant main effects and interactions will be explored using simple effects analysis. For instance, within-subject factors will be used to compare changes in outcome variables between the groups over time. A greater reduction in the total scores on MOAS in the active tDCS group than the sham tDCS group would be considered a successful primary outcome. Greater reductions in the total scores on BPI and greater increases in Stop Signal Reaction Time in the active tDCS group than the sham tDCS group would be considered successful secondary outcome. A *p* value of < 0.05 will be considered as statistically significant for the primary outcome measure. For secondary outcomes, multiple comparisons will be controlled for with Bonferroni correction and a *p* value of less than 0.0125 will be considered statistically significant.

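### The printed BPI-S frequency key gives daily the code 1, so an item that worsens from weekly to daily loses a point; probably a misprint for 3, to be corrected and checked against the form and scoring code

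*Protocol article*

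**What the plan says.** The key is in the protocol article under Outcomes {12}, Secondary outcome measures, Maladaptive behaviours. On the BPI-S that section states: "It measures frequency on a 5-point scale". The codes follow at once: "0=never/no problem, 1=monthly, 2=weekly, 1=daily, 4=hourly". The same section says how the ratings are used: "scoring yields total and domains scores for frequency for all domains". It also sets the times: "Changes in maladaptive behaviours will be measured at baseline, 1 week (day 10), and 1 month (day 38) following the last tDCS treatment".

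The direction of benefit is in Statistical methods for primary and secondary outcomes {20a}. There, "Greater reductions in the total scores on BPI" in the active arm than in the sham arm count as a successful secondary outcome, tested at 0.0125. A lower score is therefore better. No other section of the article gives a frequency key.

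**The concern.** Five categories listed in order of rising frequency should carry five rising codes. The printed key has four distinct codes, ties daily with monthly, and places daily below weekly. It thus contradicts both the stated number of points and the order of its own labels.

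The key is more than background. It says how the items of a secondary outcome are scored, and that outcome has its own success criterion. If the printed codes were copied into a data-entry form or a scoring program, some worsening would be counted as improvement and some would not register. The fault would also be hard to notice. Every code lies between 0 and 4, so a range check would pass. If only the codes were stored, monthly and daily ratings could not be told apart afterwards.

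**Working it through.** **Inputs**, all from the protocol article:
- Printed codes: never 0, monthly 1, weekly 2, daily 1, hourly 4 (Maladaptive behaviours).
- Stated number of scale points: 5 (same section).
- Direction: a reduction in total score is benefit (Statistical methods {20a}).

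**Step 1: does the key match its label?** The distinct codes are 0, 1, 2 and 4, so there are 4 codes for 5 categories. The stated 5 points are not reproduced. The only value missing from 0 to 4 is 3. The codes do not rise strictly, because 2 is followed by 1.

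**Step 2: score every worsening step.** Five categories give 5 × 4 / 2 = 10 possible worsening steps. The item change is the later code minus the earlier code. The ordered key sets daily to 3.

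| Worsening step | Printed key | Ordered key |
|---|---|---|
| never to monthly | 1 - 0 = +1 | +1 |
| never to weekly | 2 - 0 = +2 | +2 |
| never to daily | 1 - 0 = +1 | 3 - 0 = +3 |
| never to hourly | 4 - 0 = +4 | +4 |
| monthly to weekly | 2 - 1 = +1 | +1 |
| monthly to daily | 1 - 1 = 0 | 3 - 1 = +2 |
| monthly to hourly | 4 - 1 = +3 | +3 |
| weekly to daily | 1 - 2 = -1 | 3 - 2 = +1 |
| weekly to hourly | 4 - 2 = +2 | +2 |
| daily to hourly | 4 - 1 = +3 | 4 - 3 = +1 |

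Under the printed key one step has the wrong sign (weekly to daily), one scores zero (monthly to daily), and two have the right sign but the wrong size (never to daily, daily to hourly). The six steps that do not involve daily are correct. Improvements are the same steps with signs changed: daily to weekly scores +1 where the ordered key gives -1, and hourly to daily scores -3 where it gives -1. With daily set to 3, all ten worsening steps raise the score.

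**Step 3: carry it to the total.** Each item rated daily is scored 3 - 1 = 2 points too low. If D is the number of items a participant has at daily, then

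printed total = ordered total - 2 × D,

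and so

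printed change = ordered change - 2 × (change in D).

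One item moving from weekly to daily with nothing else changing gives +1 - 2 × 1 = -1. If a second item also moves from never to weekly, the ordered change is 1 + 2 = +3 and the printed change is 3 - 2 × 1 = +1, which has the right sign. The error is therefore certain for the item, while its effect on a participant's total depends on the other items.

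**The case against.** The strongest reply is that this is a plain misprint which its own sentence resolves: five labels in rising order, a stated five points, an end code of 4, and only 3 unused. The section describes an existing, cited instrument and does not announce a recoding for this trial. Care staff complete the ratings, and if they score from the instrument's own form no data are affected. Recruitment opened on July 01, 2021, before the protocol version dated January 7, 2022, so the forms may predate this text. The MOAS, its 0.05 test and the sample size do not depend on the key, nor do the BPI-S severity scores.

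Most of this stands, and it limits the weight of the point. It does not remove it. The printed key is wrong, nothing in the article corrects it, and the article does not show which codes the form or the scoring syntax uses.

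A reader might go further in two ways that the documents do not support:
- *That a participant who worsens from weekly to daily is counted as improved.* The reversal belongs to the item. The BPI-S has 30 items and success is judged on the total, which falls only if other items do not offset the error, as Step 3 shows.
- *That the secondary analysis loses a calculable amount of power or effect.* That would need the distribution of item ratings, the standard deviation of the total and its correlation over time. The article gives none of these. Eligibility asks only for one or more aggressive incidents in the last month, so how many items would be rated daily is unknown.

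**Conclusion.** The point holds as an error in the text, of minor severity. The frequency key contradicts its own label and order. Followed literally, it scores every daily rating 2 points low, reverses one of ten worsening steps and hides another.

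The effect on the between-arm comparison is -2 times the difference between arms in the mean change in the number of items rated daily. It is zero if the arms do not differ in that respect, and it cannot be sized further from the documents.

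The conclusion rests on two assumptions: that the BPI total in the success criterion is the frequency total described with the instrument, and that any effect on the data requires the printed codes to have reached the form or the scoring syntax. The evidence favours a misprint for 3=daily, and nothing in the article shows that any data have been mis-scored.

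**What to change.** In the Maladaptive behaviours section, change the code for daily from 1 to 3, so that the key reads 0, 1, 2, 3, 4. Compare the data-capture form and the scoring syntax with the corrected key, and confirm that both use five distinct rising codes. Do this before any BPI-S total is computed, including at the interim analysis planned once 30 participants have been recruited. If the form is found to carry the printed codes, go back to the recorded category labels, since a stored 1 could mean either monthly or daily.

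The cost is one digit in the protocol and a short check of the form and code. The design, the sample size and the primary analysis do not change.
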